### Preparatory Phase

In this phase, the investigator and co-investigators will form a technical advisory group, following which subject matter experts will be involved in RCT-related activities (including the final protocol and Standard Operating Procedures [SOPs] for implementing the intervention). The implementation plan will involve identifying blocks, the data collection process, quality monitoring, the safety reporting mechanism, management of adverse events, and ethical considerations. This period will also be used to recruit the project team and closely work with district stakeholders and the state government for approval of implementation.

### Intervention Phase

Following eligibility testing, children will be enrolled in one of the three groups based on stratified randomization. Baseline data of various independent and dependent variables will be captured for each child with proper screening of anthropometric measures and medical assessment. Next, each child will receive either oral amoxicillin or azithromycin and standard nutritional care (Balamrutham Plus) based on the group. In addition, based on the hemoglobin level, children with anemia at baseline will be administered iron folic acid (IFA) syrup as per Anemia Mukt Bharat guidelines [41]. Any illness during the intervention period, physician (or pediatrician) visits, treatment details, and hospitalization details will be documented during the follow-up visits.

In the amoxicillin group, amoxicillin dispersible tablet (125 mg) will be administered, along with Balamrutham Plus. The first dose will be administered upon enrollment, following by medication at home (for 5 days, twice daily). The dosage will be determined based on weight of the child, as specified by the SSFP implemented by the Government of Telangana for managing children with SAM in all districts of Telangana (Table 2) [20].

**Table 2 table2:** Dosage of amoxicillin dispersible tablets.

Weight of child (kg)	Prescription	Tablets required, n
4.0-6.9	1 tablet twice daily for 5 days	10
7.0-9.9	1.5 tablets twice daily for 5 days	15
10.0-12.9	2 tablets twice daily for 5 days	20
13.0-15.9	2.5 tablets twice daily for 5 days	25
16.0-18.9	2.5 tablets twice daily for 5 days	25

In the azithromycin group, a single dose of azithromycin syrup (20 mg/kg) will be administered, along with Balamrutham Plus.

In the control group, no antibiotics will be prescribed; only standard nutritional treatment (Balamrutham Plus) will be provided.

#### Follow-Up Visits

Children will be followed up monthly during the intervention, in addition to follow-up postdischarge from the program at 4 and 6 months. Telephone calls will be made once every 15 days to document any illness, medication use, or side effects. Physical visits will be made every 30, 60, 90, 120 and 180 days.

For compliance assessment, empty amoxicillin strips will be collected at 30 days. For azithromycin, single-dose compliance assessment will be performed on the day of enrollment to the RCT. An additional buffer of 5 days will be allowed to collect data at each timepoint. Clinical adverse events of the intervention will be assessed during physical visits and documented over the phone.

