### Study Objectives

The primary objectives of this study are as follows:

To describe the prevalence of clinical/subclinical infection and AMR patterns and determine their association with sociodemographic, clinical, and nutritional factors among children aged 6-59 months with uncomplicated SAMTo explore health-seeking behavior, antibiotic usage patterns, and care preferences among caregivers of children aged 6-59 months with uncomplicated SAM and the challenges and facilitators for health care providers in managing these childrenTo assess the efficacy of 7-day amoxicillin versus single-dose azithromycin versus no antibiotic, along with standard nutritional care, in weight gain and nutritional recovery among children aged 6-59 months with uncomplicated SAM

The secondary objective of this study is to compare medication safety (clinical adverse events) and adherence in two intervention arms (amoxicillin and azithromycin).

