Data analysis will be performed in Stata version 18.0 software using intention-to-treat analysis at the end of the study. Per protocol analysis will also be performed as a secondary analysis at the end of the study. Interim analysis will be part of the quality parameter (at the end of the first year). The WHZ and MUAC will be expressed as mean (SD) or median (IQR) with 95% CIs based on data normality. The presence of bilateral pitting edema will be expressed as proportions with 95% CIs. Independent variables (child’s age in months and mother’s age) will be expressed as mean (SD) or median (IQR) with 95% CIs based on data normality. Factors such as education status, type of delivery, and birth complications will be expressed as proportions with 95% CIs. Outcomes such as episodes of acute illness, day care absenteeism, parenteral absenteeism, number of hospital visits, and food consumption will be expressed as mean (SD) or median (IQR) with 95% CIs based on data normality. Outcomes such as the presence of sepsis and mortality status will be expressed as proportions with 95% CIs. The chi-square test will be performed to analyze the association between outcomes and categorical independent variables. An unpaired *t* test (or Mann-Whitney *U* test) will be performed to assess the association between outcomes and continuous independent variables. Poisson regression analysis (bivariate and multivariate) will be conducted to explore the association between dependent and independent factors. Adjusted risk ratios with 95% CIs will be reported for factors included in the multivariate Poisson regression model.

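### Adherence in the two antibiotic arms is measured by non-equivalent methods, and collecting only empty strips cannot quantify partial amoxicillin courses; the direction of bias is unknown

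*Protocol article*

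**What the plan says.** The secondary objective in the protocol article (Study Objectives) is to "compare medication safety (clinical adverse events) and adherence in two intervention arms (amoxicillin and azithromycin").

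The Follow-Up Visits section gives each arm its own method. For amoxicillin: "For compliance assessment, empty amoxicillin strips will be collected at 30 days". For the other arm: "For azithromycin, single-dose compliance assessment will be performed on the day of enrollment to the RCT".

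The Intervention Phase section explains how the drugs reach the child. In the azithromycin group "a single dose of azithromycin syrup (20 mg/kg) will be administered, along with Balamrutham Plus". In the amoxicillin group: "The first dose will be administered upon enrollment, following by medication at home (for 5 days, twice daily"). Table 2 sets 10, 15, 20 or 25 tablets per course by weight band, and some bands use half tablets, for example "1.5 tablets twice daily for 5 days".

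Two other statements bear on the point. Follow-Up Visits adds: "Telephone calls will be made once every 15 days to document any illness, medication use, or side effects". Data Entry and Analysis, Phase 3, adds: "Per protocol analysis will also be performed as a secondary analysis at the end of the study". Adherence is not in the Outcomes list, and the Phase 3 analysis text names no adherence analysis.

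**The concern.** A comparison between arms is interpretable only if the same quantity is measured in both. Here one arm is assessed on the day its single dose is due. The other is assessed about 25 days after a five-day home course has ended, from packaging that families have kept.

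The amoxicillin rule is also incomplete on its own terms. Leftover tablets are the direct evidence of missed doses, and they sit in partly used or unused strips, which the rule as worded does not collect. An empty pocket shows that a tablet left the strip, not that the child swallowed it. A strip that is not returned may mean an incomplete course or simply a lost strip, and the stated rule cannot separate the two.

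What is at stake is a stated secondary objective, any per-protocol population that relies on adherence, and part of the policy message: the Conclusion section names better adherence among the operational advantages that single-dose azithromycin may offer.

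**Working it through.** The article gives no adherence rate, threshold or precision target, so there is no planned figure to reproduce. The check sets the two methods side by side and then asks which way the measurement error could run.

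**1. The two methods**

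| | Azithromycin | Amoxicillin |
|---|---|---|
| Doses in the course | 1 | 5 days x 2 = 10 |
| Where given | At enrolment (implied) | First at enrolment; 10 - 1 = 9 at home, if the first counts towards the course |
| When assessed | Enrolment day | Day 30, plus up to 5 days |
| Lag after the last dose | None | About 30 - 5 = 25 days, up to 30 with the window |
| Evidence | Compliance check that day | Empty strips |

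**2. Half tablets.** Three of the five bands in Table 2 (7.0-9.9, 13.0-15.9 and 16.0-18.9 kg) use 1.5 or 2.5 tablets per dose. Over 10 doses that is 15 or 25 tablets, so a child who takes everything uses exactly the Table 2 quantity. A half that is removed and not taken leaves the same empty pocket as one that is swallowed.

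**3. Telephone calls.** The first is at day 15, about 10 days after the course ends. Follow-Up Visits says that the calls record medication use; Table 1 lists adverse-event symptoms, illness and treatment details. Neither names study-drug doses.

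**4. Direction of error (all rates assumed).** Let *t* be the true full-course rate on amoxicillin, *se* the share of full-course children whose strips all come back empty, and *fp* the share of incomplete-course children whose strips also come back empty. Count a child as adherent when all strips come back empty. Then

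measured rate *m* = *t* x *se* + (1 - *t*) x *fp*

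and the error is *m* - *t* = (1 - *t*) x *fp* - *t* x (1 - *se*). The first term overstates amoxicillin adherence and the second understates it.

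With azithromycin at 99% and *t* = 80%, the true gap is 99 - 80 = 19 points:

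| *se* | *fp* | Measured amoxicillin | Observed gap (points) |
|---|---|---|---|
| 1 | 0 | 0.80 + 0 = 80% | 19 |
| 1 | 0.5 | 0.80 + 0.10 = 90% | 9 |
| 1 | 0.9 | 0.80 + 0.18 = 98% | 1 |
| 1 | 1 | 0.80 + 0.20 = 100% | -1 |
| 0.8 | 0 | 0.64 + 0 = 64% | 35 |
| 0.8 | 0.5 | 0.64 + 0.10 = 74% | 25 |

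For *t* from 60% to 90%, the true gap runs from 99 - 60 = 39 down to 99 - 90 = 9 points. Over the same six settings the observed gap runs from -1 (*se* = 1, *fp* = 1, any *t*) to +51 (*t* = 60%, *se* = 0.8, *fp* = 0: 0.60 x 0.8 = 48%, and 99 - 48 = 51). The measurement can shrink, erase or inflate the difference, and nothing in the article indicates which.

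**The case against.** The strongest reply is that one dose at enrolment really is easier to complete than ten doses, most of them at home. A higher azithromycin rate would then be a property of the regimen, not an artefact. This stands. A reader might infer that the design must favour azithromycin, but the documents do not support that: empty strips can overstate amoxicillin adherence and narrow the gap, while lost strips can widen it. Nor is an arm difference obtained by subtracting an assumed true amoxicillin rate from 100% a measure of bias; it is only the assumed true difference.

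Four further limits also stand:

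- Observed azithromycin dosing is implied by the text, not stated.
- No formal adherence test is specified. The objective asks for a comparison, which a descriptive report would satisfy.
- The per-protocol set is not defined in the article and is not tied to strips.
- It would be too strong to say that partial courses go unmeasured. A strip that fails to come back empty is a signal of some kind, and the calls might be used to ask about study drug.

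The last line of defence is that strip handling belongs in the standard operating procedures, which the Preparatory Phase section mentions. That would answer a complaint about missing detail. Here, however, the article states a collection rule, and that rule names empty strips only. If the procedures already require full retrieval and a tablet count, the article should say so.

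**Conclusion.** The point holds in limited form. The two antibiotic arms are to be compared on adherence with methods that do not measure the same thing, and the amoxicillin method as worded cannot quantify a partial course. The comparison, and any per-protocol set based on adherence, is not like for like.

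The size and sign of the bias cannot be derived from the article. The range of -1 to +51 points against true gaps of 9 to 39 is an illustration. It rests on the assumed 99% for azithromycin, true full-course amoxicillin rates of 60-90%, and the assumed strip-return patterns. The conclusion that the methods are not equivalent needs none of those values.

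The consequence is confined to a secondary objective and possibly a secondary analysis; the intention-to-treat comparison of the primary outcomes does not depend on it. It is still worth correcting, because the remedy is cheap and the Results section reports that the randomised component has been delayed, so the form can be changed before trial data accrue.

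**What to change.** Replace the strip rule in Follow-Up Visits and adjust the reporting:

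- At the day-30 visit, collect every dispensed strip, whether empty, partly used or unused, and count the remaining tablets. Record a strip that is not returned as such.
- Compute amoxicillin adherence as tablets used divided by the Table 2 quantity dispensed. Supplement it with caregiver-reported doses, for example through a specific question at the day-15 call.
- Record azithromycin as dose given and observed, yes or no.
- Report adherence descriptively by arm and state that the methods differ.
- If the per-protocol definition uses adherence, base the amoxicillin part on the tablet count.

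The denominator depends on course length. Study Objectives gives seven days of amoxicillin, while Intervention Phase and Table 2 give five; those passages must be reconciled before the form is fixed.

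The cost is slightly more form work at a visit that is already planned and one added question on an existing call. No treatment, visit or sample size changes.

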### Operational Definitions

Children with uncomplicated SAM are clinically well (ie, without signs of infection) and with a retained appetite (passed the appetite test), which is considered indicative of the absence of severe metabolic disturbance. SAM is defined as WHZ<–3 SD of the median WHO child growth standards and/or by the presence of bilateral pitting edema. Nonresponse to treatment is defined as children who do not meet discharge criteria (WHZ>–2 SD) after 4 months.

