## Introduction

### Background

Acute malnutrition is defined as a condition characterized by a severe nutrient deficit due to inadequate intake of food or the inability of the body to properly absorb essential nutrients [1]. Worldwide, 45.4 million children aged <5 years have wasting [2]. In India, the National Family Health Survey (NFHS)-5 reported a 19.3% burden of wasting and a 7.7% burden of severe wasting [3]. Although the burden of wasting remains almost constant, there is an increase in severe wasting compared to NFHS-4 and NFHS-3 [3-5]. Severe wasting indicates severe acute malnutrition (SAM) and is defined as a weight-for-height z-score (WHZ) of <−3 SD, a mid-upper arm circumference (MUAC) of <115 mm, or bilateral pitting pedal edema [6].

From the management perspective, SAM is further classified into complicated and uncomplicated SAM. Children with complicated SAM exhibit no appetite or have medical complications, while those with uncomplicated SAM have a successful standard appetite test and no fever, clinical infections, or complications [7]. Children with both complicated and uncomplicated SAM have a higher risk for acute infections, such as pneumonia, diarrhea, and sepsis, which triples the mortality risk: a few reported reasons are a weakened immune system, altered gut microbiota, poverty, food insecurity, and inadequate access to health care [8,9]. The fatality rate among children with SAM receiving inpatient care ranges from 3.4% to 35%. These data show that 3.5 million deaths are estimated among children in India aged <5 years [10].

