### Inclusion and Exclusion Criteria

#### Phase 1

The inclusion criteria are (1) age 6-59 months, (2) both sexes, (3) resident of the study area, (4) WHZ≤–3 SD without any signs of complications (uncomplicated SAM), and (5) passing the appetite test.

Children with SAM who have medical complications or infection have loss of appetite due to underlying physiological changes. The appetite test helps identify such children. Every child identified as having SAM during growth monitoring will undergo the appetite test to decide the further course of treatment. In Telangana, Balamrutham Plus is used under the SSFP for the test. The quantity provided varies by age: age 7-18 months, at least 15 g; age 19-36 months, 30 g; and age 37-59 months, 50 g. Children who are able to consume the given quantity are considered to have passed the test and are enrolled in the SSFP; otherwise, they are referred to a nutrition rehabilitation center for further treatment. The test usually takes a short time but may even take up to 1 hour [20].

The exclusion criteria are (1) WHZ≥–2 SD, between –2 SD and –3 SD, or <–3 SD with complications (children with complicated SAM); (2) bilateral pitting edema; (3) congenital anomalies, inborn errors of metabolism, or developmental delay; and (4) malabsorption syndromes.

Children with SAM will be identified from the NHTS through the district health administration. During the study period, all eligible children will be contacted to participate in the study.

#### Phase 2

Primary caregivers of children aged 6-59 months with uncomplicated SAM will be identified based on their volunteerism and participation. Each FGD will include 8-10 participants, and 10-12 FGDs will be conducted, in addition to 2 IDIs in each health care worker group: ASHA, *Anganwadi* teacher (center), ANM (subcenter), MO (PHC), and pediatrician (district hospital and tertiary care center). The number of FGDs and IDIs will be based on the level of information saturation.

#### Phase 3

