**Figure 1 figure1:**
[figure not shown]
RCT CONSORT flow diagram for recruitment, follow-up, and endline assessment of participants in the study. CBC: complete blood count; CONSORT: Consolidated Standards of Reporting Trials; DST: drug susceptibility testing; ESR: erythrocyte sedimentation rate; FGD: focus group discussion; hs-CRP: high-sensitivity C-reactive protein; IDI: in-depth interview; RCT: randomized controlled trial; SAM: severe acute malnutrition.

**Table 1 table1:** Timepoints and activities to be carried out during the study.

Activity	Baseline	Enrollment to RCT^a^ (within 7 days of collecting baseline data)	Telephonic follow-up at 15, 45, 75, and 105 days (plus 5 days allowed at each timepoint)	Physical follow-up at 30, 60, 90, 120, and 180 days (plus 5 days allowed at each timepoint)
Consent; appetite test; sociodemographic, nutritional, and health-related information obtained through questionnaires during face-to-face interviews + 4 mL^b^ of blood sample, urine sample, and stool sample for CBC^c^, ESR^d^, culture, DST^e^, hs-CRP^f^, procalcitonin, and anthropometry (height, weight, MUAC^g^)	✓	—^h^	—	—
RCT eligibility assessment, randomization and antibiotic distribution, and IFA^i^ syrup distribution in the case of anemia	—	✓	—	—
Weight, height, MUAC, symptoms of adverse events, any illness, and treatment details	—	—	—	✓
Symptoms of adverse events, any illness, and treatment details	—	—	✓	✓

^a^RCT: randomized controlled trial.

^b^Biological samples will be collected from 606 study participants.

^c^CBC: complete blood count.

^d^ESR: erythrocyte sedimentation rate.

^e^DST: drug susceptibility testing.

^f^hs-CRP: high-sensitivity C-reactive protein.

^g^MUAC: mid-upper arm circumference.

^h^Not applicable.

^i^IFA: iron folic acid.

#### Phase 1

A list of children with uncomplicated SAM will be obtained from the NHTS website through district stakeholders. The children will be visited at their homes to confirm their diagnosis and malnutrition category and will be enrolled into the study after obtaining informed consent from the caregivers. The children’s sociodemographic, nutritional, and health-related information will be obtained through questionnaires and interviews. Under a sterile environment, 4 mL of blood sample will be taken from each child. Two sterile containers will be given to the children to collect urine and stool samples, and those samples will be collected from the caregivers the following day.

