### Data Entry and Analysis

#### Phase 1

Data will be entered into the Epicollect5 mobile app and analyzed in Stata version 18.0 software. Continuous variables (age, weight, height, WBC count, ESR, hs-CRP, procalcitonin, and colony-forming units) will be expressed as mean (SD) or median (IQR) based on data distribution. Categorical variables (clinical infection, subclinical infection, and AMR) will be expressed as percentages. The association between independent factors (sociodemographic, health, and nutritional factors) and of clinical/subclinical infection and AMR outcomes will be analyzed using chi-square tests, *t* tests, or Mann-Whitney *U* tests. Multivariate analysis using log-binomial regression will be performed to adjust for confounders. *P*<.05 will be considered statistically significant.

#### Phase 2

English transcripts will be prepared within 24 hours of conducting an IDI/FGD. Qualitative data will be analyzed in Atlas Ti software. First, complete transcripts will be read by the investigators to ensure immersion, initial codes will be generated inductively using inductive coding in Atlas.ti software, and the codes will be iteratively refined through discussions and organized into subcategories (subthemes) and higher-order categories (themes) in line with reflexive thematic analysis principles [42]. An audit trail (coding decisions, evolving codebooks, and notes from analytical discussions) will be maintained throughout the process to support confirmability and dependability. We will also perform data triangulation of qualitative and quantitative data to increase the credibility of the information collected about knowledge, barriers, and facilitators related to antibiotic usage among children with uncomplicated SAM by adopting convergent parallel mixed methods design.

#### Phase 3

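### Phase 1 sets out to estimate and model clinical infection in children whose eligibility definition excludes it

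*Protocol article*

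**What the plan says.** Who is enrolled in Phase 1:

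- Background: "those with uncomplicated SAM have a successful standard appetite test and no fever, clinical infections, or complications".
- Operational Definitions: "Children with uncomplicated SAM are clinically well (ie, without signs of infection) and with a retained appetite (passed the appetite test".
- Inclusion and Exclusion Criteria, Phase 1: the child must have WHZ≤–3 SD "without any signs of complications (uncomplicated SAM") and must pass the appetite test. The same section describes that test as a help in finding children with complications or infection. The four Phase 1 exclusions name neither fever nor infection.
- Study Procedure, Phase 1: "The children will be visited at their homes to confirm their diagnosis and malnutrition category". Enrolment follows this visit.

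What is estimated in them:

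- Study Objectives: "To describe the prevalence of clinical/subclinical infection and AMR patterns and determine their association with sociodemographic, clinical, and nutritional factors".
- Outcomes: the exploratory list has one proportion for clinical infection, from clinical evaluation, and a separate one for subclinical infection, from hs-CRP, procalcitonin, blood culture and urine culture.
- Data Entry and Analysis, Phase 1: "Categorical variables (clinical infection, subclinical infection, and AMR) will be expressed as percentages"; and, for the associations with infection and AMR, "Multivariate analysis using log-binomial regression will be performed to adjust for confounders".
- Sample Size, Phase 1: 606 children, planned on a 50% prevalence of lower respiratory tract infection in uncomplicated SAM. The preceding sentence cites a range of 15% to 68% for clinical infection in complicated SAM.

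**The concern.** The condition to be counted is one that the definition of the study population removes. If field staff apply the definition, a child with clinical infection is not enrolled, and any case that appears in the data is a departure from it. If staff apply only the inclusion criterion as worded, some children with mild signs may enter, and the result then measures screening practice as well as disease.

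This bears on what Phase 1 can conclude. The Rationale of the Study says that the relevance of empirical antibiotics is to be judged from infection rates in these children when they are identified, and Strengths and Limitations links the findings to possible revision of guidelines. A low clinical figure that selection produced could be read as evidence that infection is rare. The Results section says that Phase 1 has been initiated, and clinical findings in children turned away cannot be recovered later unless they are logged at the visit.

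**Working it through.** **1. The plan's own sample size.** Inputs from Sample Size, Phase 1: p = 0.50; 10% relative precision, so d = 0.05; design effect printed as 1.5% and read as 1.5; nonresponse 10%; type I error 5%.

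- n0 = 1.96² × 0.50 × 0.50 / 0.05² = 384.15
- × 1.5 = 576.2
- With 10% nonresponse: 576.2 / 0.90 gives 641, and 576.2 × 1.10 gives 634
- With 5% nonresponse: 576.2 / 0.95 gives 607, and 576.2 × 1.05 gives 606

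So 606 is not reproduced at the stated 10% nonresponse, and it matches 5%. That is a separate matter, and the present point does not depend on it. What matters here is that 606 was built on p = 0.50 for a clinical infection.

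**2. Clinical events implied by different parts of the protocol, out of 606.**

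| Basis | Assumed prevalence | Expected events |
|---|---|---|
| Background and Operational Definitions | 0 | 606 × 0 = 0, plus any misclassified children |
| Sample Size, Phase 1 | 50% | 606 × 0.50 = 303 |

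Both cannot describe the same children. The precision target also fails under the first row, since a relative precision has no meaning around an expected proportion of zero.

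**3. The looser reading of the inclusion criterion.** The protocol gives no rate for mild signs in children who would pass it. Purely as an assumption, the section on the need for a control group cites NFHS-5 figures of 2.8% for acute respiratory infection and 7.3% for diarrhea. Applied to 606 these give 606 × 0.028 ≈ 17 and 606 × 0.073 ≈ 44. The count could lie anywhere from 0 upward, depending on which signs are let through.

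**4. Outcomes that the definition does not touch.** Subclinical infection is determined in the laboratory. At the 35% assumed in Study Procedure, Phase 3, expected events are 606 × 0.35 ≈ 212, or 545 × 0.35 ≈ 191 if 10% do not respond. AMR is also a laboratory outcome; the protocol gives no planning rate for it.

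**5. The model.** A log-binomial regression on clinical infection alone has no events under the definition and cannot be fitted. With a few misclassified cases, its risk ratios would describe who slips through screening. The regressions on subclinical infection and AMR do not have this problem.

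**The case against.** The strongest reply is that the operative Phase 1 criterion speaks of complications, that no exclusion names fever or infection, and that the appetite test is described only as a help in finding infected children. On that reading a nonzero clinical count is plausible. This stands as far as it goes: a reader might infer that the prevalence is exactly zero by rule, and the documents support that only if the operational definition is read into the inclusion criterion. But the criterion itself attaches the term uncomplicated SAM, which the protocol defines twice as free of clinical infection. If the looser wording governs, the two sections conflict and the estimand is undefined.

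A second reply is that infection found among children carrying the programme's label is informative, because it tests whether the label holds. That is right. It argues for counting infection in all listed children before the study removes any, and not in those left after confirmation.

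A third is that the programme list already consists of uncomplicated cases, and that children who fail the appetite test are referred elsewhere. This also stands. A tally at the home visit gives prevalence among programme-listed children and cannot be presented as prevalence in all community SAM.

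Finally, a reader might infer that the Phase 1 regression as a whole lacks events. It does not: clinical infection is one of three outcomes, and subclinical infection alone should supply roughly 190 to 212.

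**Conclusion.** The concern holds for the clinical-infection component of Phase 1 and no further. The definition, the inclusion criterion, the objective and the planning assumption cannot all stand: they imply an expected clinical count of zero, a number set by screeners' tolerance, or 303 of 606. One named part of the first objective and one listed outcome therefore cannot be interpreted as written. Subclinical infection, AMR and their regressions are unaffected, and the randomized phase stratifies on subclinical status only.

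The zero rests on applying the operational definition at enrolment; the 303 rests on the protocol's 50%. No confidence limit is attached to the zero, because a figure fixed by selection has no sampling uncertainty of that kind. Nor is the distance from the 15% to 68% range a measure of loss, since that range belongs to complicated SAM. The conflict lies between statements that the article makes outright, so an unseen analysis plan would not by itself remove it.

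**What to change.** 1. Reconcile the Phase 1 inclusion criterion, the operational definition and the 50% assumption in Sample Size. State whether children with signs of infection can be enrolled, and whether the clinical evaluation that feeds the outcome takes place before or after eligibility is confirmed.
2. Report clinical infection among all programme-listed children with WHZ≤–3 SD who are examined at the confirming home visit, before the study's exclusions. Label it as prevalence among programme-listed children, not among all community SAM.
3. Report subclinical infection and AMR among enrolled children, as now.
4. Remove clinical infection as a modelled outcome in the enrolled group, and reword the objective and outcome list to show the two denominators.
5. If the sample-size paragraph is re-anchored on subclinical infection at 35%, restate the precision. With 606 children and a design effect of 1.5 the half-width is 1.96 × √(1.5 × 0.35 × 0.65 / 606) = 0.0465, which is 13.3% relative.

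The cost is small, because the visits already take place. The downside is that the screening log must record clinical findings for children who are not enrolled, so the consent arrangements, which now come after the confirming step, need to cover that record. As Phase 1 has started, the log should change soon.
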